**5.5 EXPECTEDNESS**

Expectedness should be assessed by the PI at site and the CI determining as to whether the SAE is in direct response to the study procedures.

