**5.1.2 Serious Adverse Event (SAE)**

An SAE is defined as any untoward and unexpected medical occurrence or effect that

• results in death,

• is life threatening – refers to an event in which the participant was at risk of death at the time of the event. It does not refer to an event which hypothetically might have caused death if it were more severe,

• requires hospitalisation or prolongation of existing inpatient hospitalisation,

• results in persistent or significant disability or incapacity

• Is a congenital anomaly or birth defect, and

• Is otherwise considered medically significant by the investigator

Medical judgement should be exercised in deciding whether an AE is serious in other situations. Important AEs that are not immediately life‐threatening or do not result in death or hospitalisation but may jeopardise the participant or may require intervention to prevent one of the other outcomes listed in the definition above, should also be considered serious.

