**5.2 REPORTING PROCEDURES**

All AEs for this study will be recorded at each study visit on the study case report form (CRF). This study does not require the formal reporting of any non-serious AEs. This is a non-interventional study. We therefore do not anticipate a large number of SAEs.

Investigators must report all SAEs from enrolment to the end of the study. In addition, maternal death and maternal life-threatening complications, stillbirths and neonatal deaths are also pre-specified outcomes to be reported immediately as SAEs. All deaths reported as SAEs as part of this study will be reviewed regularly by the SMG and Sponsor. Urgent reporting of any SAEs in relation to the study medical device or study procedures are required. All SAEs must be reported within 24 hours of sites becoming aware of the event. Reporting should be completed by downloading the XXX study SAE form from the study file repository within REDCap, completing all fields on the form and then send it to the Study Co-Ordinator at the CfWHR. All SAE’s will be subject to regular review by the SMG.

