**5.6.2 Guidance on Reporting Serious Adverse Events**

The CASPAR SAE form can be downloaded from the study management portal. This should be completed by the Investigator at site. The Investigator should assess the SAE in terms of severity, causality / relatedness and expectedness. They should assess expectedness as to whether the SAE is in direct response to study procedures.

In the absence of the PI, the SAE form should be completed by a designated member of the site clinical research team (as detailed on the site delegation log). The responsible individual should complete a final check of the SAE form, ensuring that all fields are complete and accurate – including no personal information relating to the study participant. Once this is confirmed, they should sign and date the form and forward to the CASPAR Study coordinator at the CfWHR. Immediate reporting of SAE forms can be via:

1. email to the CASPAR secure email account at TBC, or

2. Fax to CASPAR Study Co-Ordinator, CASPAR Management Team, Centre for Women’s Health Research, Department of Women’s and Children’s Health, University of Liverpool [name].

For urgent safety queries and where both fax and email systems have failed, please contact the CASPAR Study Co-Ordinator on (TBC)

An acknowledgement for all SAE reports will be sent to the site on the same day as the receipt of the report (where receipt is Monday – Friday, 9:00 – 17:00. For out of hours, weekends and bank holidays an acknowledgement will be sent by 11:00 on the next working day. Please note – if no acknowledgement is received by the site within the timeframes set out here, they should contact the Centre for Women’s Health Research on [name] to confirm the SAE report has been received.

Following the completion of the SAE form and forwarding this to the Study Management team (as set out above); the PI must then notify their relevant R&D Department of the event, as per their standard local procedure.

In the event that an SAE requires follow-up, this should confirm that recovery is complete and the participant has returned to normal or stabilised. Follow-up information should be provided on the same CASPAR SAE form Additional supporting copies of test results can be provided separately.

The Investigator at site should ensure that the participant must be identified only by their unique study identification number and date of birth. The participants’ personal information must not be included on any correspondence.

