All investigators must ensure that multiple SAEs are reported separately on different forms - one report should be provided for each overall diagnosis.

Reports of related or unexpected SAEs should be submitted to the Sponsor and REC by the Study Co-Ordinator within 15 days of the CI and Study Co-Ordinator becoming aware of the event. This report should be completed on the NRES SAE form for non-IMP studies.

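### The protocol makes being unexpected part of the SAE definition and then defines expectedness by causation, so some serious procedure-related events can miss expedited reporting

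*Protocol*

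**What the plan says.** Four rules in section 5 of the protocol bear on the point.

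- **Definition (5.1.2).** "An SAE is defined as any untoward and unexpected medical occurrence or effect that" meets one of the listed seriousness criteria. A closing clause asks for medical judgement and lets other important events be treated as serious; that clause does not mention expectedness.
- **Expectedness (5.5 and 5.6.2).** Under 5.5 the site PI assesses it, with "the CI determining as to whether the SAE is in direct response to the study procedures". Section 5.6.2 says the same of the investigator: "They should assess expectedness as to whether the SAE is in direct response to study procedures". Yet 5.6.2 also lists expectedness as separate from causality: "The Investigator should assess the SAE in terms of severity, causality / relatedness and expectedness". Causality has its own five-level scale in 5.4 (Table 2).
- **Site reporting (5.2).** "All SAEs must be reported within 24 hours of sites becoming aware of the event", and "Urgent reporting of any SAEs in relation to the study medical device or study procedures are required". Non-serious events need no formal report. Maternal death, maternal life-threatening complications, stillbirth and neonatal death are reported as SAEs in any case.
- **Onward reporting (5.6.2 and 5.6.3).** "Reports of related or unexpected SAEs should be submitted to the Sponsor and REC by the Study Co-Ordinator within 15 days". That period runs from when the CI and coordinator learn about it. Section 5.6.3 adds that every SAE goes to the Sponsor, REC and HRA as regulation requires.

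**The concern.** Seriousness, relatedness and expectedness are normally three separate judgements: how bad the event was, whether the study procedure caused it, and whether it could have been foreseen. Here the third is built into the first and given the content of the second.

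The reporting duties in 5.2 attach to the label SAE, so an event that loses the label loses the duties. The events most open to this are those the safety rules most need to see: serious events caused by the aspiration probe or the speculum examination, or foreseeable from them. The study has no independent safety committee (8.2). Oversight rests on the Study Management Group and the Sponsor, and much of what they see is SAE listings and reports produced every three months (5.6.3, 10.4.4). What enters those listings depends on how each investigator reads one word.

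**Working it through.** No figure in the plan is involved, so the check sets the rules against each other. Take an event that meets one of the listed seriousness criteria and classify it two ways: related to the study procedure or not, and foreseeable or not. That gives four classes. Apply the opening sentence of 5.1.2 under each meaning that *unexpected* could have.

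| Serious event | Ordinary meaning: not foreseeable | 5.5/5.6.2 meaning: not a direct response to procedures | Mirror meaning: a direct response to procedures |
| --- | --- | --- | --- |
| Related, foreseeable | not an SAE | not an SAE | SAE |
| Related, not foreseeable | SAE | not an SAE | SAE |
| Unrelated, foreseeable | not an SAE | SAE | not an SAE |
| Unrelated, not foreseeable | SAE | SAE | not an SAE |
| Classes that qualify | 2 of 4 | 2 of 4 | 2 of 4 |

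The middle column takes an event that is a direct response to procedures as *expected*. The mirror column takes it as *unexpected*. Sections 5.5 and 5.6.2 do not say which answer means which.

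**Step 1, the definition.** On the ordinary meaning, a foreseeable serious event due to the procedure, such as one that lengthens the hospital stay, is not an SAE. On the 5.5/5.6.2 meaning, no event directly caused by the procedure is one. The latter cannot stand beside 5.2, which requires urgent reports of SAEs linked to the device or procedures. The mirror meaning keeps procedure-caused events but drops every unrelated serious event.

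**Step 2, what an excluded event misses.** The 24-hour rule, the urgent device rule and the 15-day rule are all worded for SAEs, so all three are missed. Two provisions bring some events back: the deaths and maternal life-threatening complications named in 5.2, and the judgement clause at the end of 5.1.2. What is left exposed is a serious event that neither catches.

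**Step 3, the 15-day rule.** It passes an SAE that is related or unexpected.

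- With 5.1.2 applied and one meaning used throughout, every SAE is already unexpected, so all pass.
- With 5.1.2 set aside and the 5.5/5.6.2 meaning used, the rule reads *related, or not a direct response*. Every event is one or the other: 4 of 4 classes pass.
- With 5.1.2 set aside and the mirror meaning used, the rule reads *related, or a direct response*. That is simply *related*: 2 of 4 pass.

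In the first two cases the rule selects nothing. In the third it selects on relatedness alone. Expectedness adds no information in any of them.

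**Step 4, after repair.** If seriousness does not depend on expectedness, and expectedness means foreseeability, all 4 classes can be SAEs. *Related or unexpected* then passes 3 of 4 (all but unrelated and foreseeable), and *related and unexpected* would pass 1 of 4. Either rule discriminates.

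The fractions count classes of event. They are not frequencies.

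**The case against.** The strongest reply is that little is lost in practice. All adverse events go on the CRF (5.2, 5.6.1), severity is graded whether or not an event is serious (5.3), and the Study Management Group reviews adverse events regularly (10.4.4). The gravest outcomes are reportable regardless, and the judgement clause may catch others. A 15-day rule that passes everything errs towards over-reporting, and 5.6.3 already sends all SAEs onward. A direct response is also narrower than *possibly* or *probably* related in Table 2, so the two tests are not identical. The risk assessment is low (10.1), the documents name no foreseeable serious device harm, and none of the four feasibility outcomes in 3.2 is a safety measure, although its introduction mentions safety.

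Most of this stands and limits the point. It does not remove the conflict. The narrower sense of direct response leaves Step 3 unchanged, because anything that is a direct response is also related; and in Step 1 directly caused events still drop out on the 5.5/5.6.2 meaning. CRF recording does not replace 24-hour reporting.

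A reader might go further in three ways that the documents do not support.

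- *That device harm would go uncounted.* It would still be recorded and reviewed as an adverse event; what can be lost is SAE status and expedited reporting.
- *That the SAE count could run from about 0 to about 20 by reading alone.* Section 1.1 says almost 20% of inductions end in unplanned caesarean, and 100 × 20% = 20. But that rate is for inductions in general and this cohort is primiparous. Nothing says that each caesarean is an untoward event or prolongs the stay. The lower end is not zero by rule either, since the events named in 5.2 and truly unexpected events still count.
- *That expecting few SAEs (5.2) conflicts with that caesarean rate.* Under 5.1.2 as written, a foreseeable caesarean is not an SAE, so few SAEs is what the text predicts.

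**Conclusion.** The point holds as a contradiction in the stated rules. Expectedness is a condition of being an SAE in 5.1.2 and a causal test in 5.5 and 5.6.2, although relatedness is graded separately in 5.4. Of the two related classes of serious event, the definition excludes one on the ordinary meaning and both on the 5.5/5.6.2 meaning. The practical exposure is narrow: serious events that are foreseeable or caused by the procedure, are not among the outcomes named in 5.2, and are not rescued by the judgement clause. For these, expedited reporting can be missed; it will not necessarily be. The fault in the 15-day rule cannot by itself cause under-reporting of SAEs.

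No number of affected women can be derived, and no planned estimate in section 6 changes. The conclusion assumes a literal reading of section 5. The SAE form and the device's instructions for use are not in the document, so either may already list expected effects; that would help investigators but would not reconcile the protocol text. The amendment should be made, because it is cheap and concerns safety reporting.

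**What to change.** Reconcile 5.1.2, 5.2, 5.5, 5.6.2 and 5.6.3 in one amendment:

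1. Remove the words requiring an SAE to be unexpected from 5.1.2, so that seriousness rests on the listed criteria alone.
2. In 5.5 and 5.6.2, define expectedness by whether the event was foreseeable, judged against a written reference such as the device's instructions for use, and keep it separate from the relatedness grade in 5.4.
3. State once which SAEs go to the Sponsor and REC within 15 days, naming the combination of relatedness and expectedness that triggers the report, and align 5.6.3 with it.
4. Because step 1 widens the SAE definition, state how obstetric and neonatal events already collected as outcomes in 6.3 are to be handled in SAE reporting.

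The same amendment can correct two cross-references: 5.3 points to section 8.1 for the seriousness criteria, which are in 5.1.2, and 5.4 cites a table 3 where the relatedness scale is Table 2.

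The cost is a wording change to section 5 and, where needed, the SAE form, with a briefing for site staff. Sample size, procedures and analyses are unaffected.

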**5.6 REPORTING**

Any questions concerning AE reporting should be directed to the Study Co-Ordinator in the first instance.

**5.6.1 Non Serious Adverse Events**

All AEs should be reported on the study CRF at the time of assessment (please see study schedule).

**5.6.2 Guidance on Reporting Serious Adverse Events**

The CASPAR SAE form can be downloaded from the study management portal. This should be completed by the Investigator at site. The Investigator should assess the SAE in terms of severity, causality / relatedness and expectedness. They should assess expectedness as to whether the SAE is in direct response to study procedures.

In the absence of the PI, the SAE form should be completed by a designated member of the site clinical research team (as detailed on the site delegation log). The responsible individual should complete a final check of the SAE form, ensuring that all fields are complete and accurate – including no personal information relating to the study participant. Once this is confirmed, they should sign and date the form and forward to the CASPAR Study coordinator at the CfWHR. Immediate reporting of SAE forms can be via:

1. email to the CASPAR secure email account at TBC, or

2. Fax to CASPAR Study Co-Ordinator, CASPAR Management Team, Centre for Women’s Health Research, Department of Women’s and Children’s Health, University of Liverpool [name].

For urgent safety queries and where both fax and email systems have failed, please contact the CASPAR Study Co-Ordinator on (TBC)

An acknowledgement for all SAE reports will be sent to the site on the same day as the receipt of the report (where receipt is Monday – Friday, 9:00 – 17:00. For out of hours, weekends and bank holidays an acknowledgement will be sent by 11:00 on the next working day. Please note – if no acknowledgement is received by the site within the timeframes set out here, they should contact the Centre for Women’s Health Research on [name] to confirm the SAE report has been received.

Following the completion of the SAE form and forwarding this to the Study Management team (as set out above); the PI must then notify their relevant R&D Department of the event, as per their standard local procedure.

In the event that an SAE requires follow-up, this should confirm that recovery is complete and the participant has returned to normal or stabilised. Follow-up information should be provided on the same CASPAR SAE form Additional supporting copies of test results can be provided separately.

The Investigator at site should ensure that the participant must be identified only by their unique study identification number and date of birth. The participants’ personal information must not be included on any correspondence.

All investigators must ensure that multiple SAEs are reported separately on different forms - one report should be provided for each overall diagnosis.

Reports of related or unexpected SAEs should be submitted to the Sponsor and REC by the Study Co-Ordinator within 15 days of the CI and Study Co-Ordinator becoming aware of the event. This report should be completed on the NRES SAE form for non-IMP studies.

**5.6.3 Additional Reporting**

All SAEs will be reported to Sponsor, REC and the HRA in line with regulatory requirements. Line listings will be provided to PIs and Sponsor on a three-monthly basis: these will also be provided to the SMG. All SAEs will be reviewed as part of central monitoring by the SMG.

**6. STATISTICS AND DATA ANALYSIS**

**6.1 INTRODUCTION**

In the following section a brief overview of planned analyses for this study will be set out.

Once informed consent has been gained for participation in CASPAR participants will be registered onto the study database and a unique PIN will be generated. Participants will be registered onto the study database in accordance with the study registration operating procedures and registration will be performed by authorised CASPAR research staff using an electronic system. This system will be available 7 days per week, 24 hours a day and will be accessed by delegated site staff using a secure password protected website. All research staff will receive comprehensive training on the use of this system, which will be documented and stored in the Investigator Site File (ISF). In the unlikely event that the back-up registration process is activated, participant registration will be performed by the Study Co-Ordinator.

Data from the CASPAR CRFs will be entered onto a bespoke study database with extensive data validation checks alerting all missing data to be queried. Missing data will be monitored and strategies will be developed to minimise its occurrence. Central statistical data monitoring will summarise missing or inconsistent data periodically. The study CRF will be approved by the CI and validations will also be made that will cross check the study CRF with the CASPAR study database.

**6.2 SAMPLE SIZE**

LWH has 14 available induction of labour appointments available per day for both inpatient and outpatient inductions. We anticipate at least 50% of patients attending to meet eligibility for this study. We hope to achieve a recruitment rate of 50% from this patient group. Over a 12-month period, we would therefore conservatively expect to recruit 100 women.

As this is an exploratory piece of work a formal sample size calculation has not been performed.

**6.3 OUTCOME MEASURES**

Feasibility outcomes will be collected as outlined in section 3.2

The primary clinical outcome will be vaginal delivery.

Secondary maternal and neonatal outcomes will be recorded for descriptive analyses:

- Maternal outcomes; induction to delivery interval, induction agent(s), category of caesarean section if undertaken, indication for caesarean section if undertaken, oxytocin use, tocolytic use, epidural analgesia use, estimated blood loss, obstetric anal sphincter injury, instrumental delivery
- Neonatal outcomes; stillbirth or neonatal death, apgar score <7 at 5 minutes, NICU admission, infant requiring cooling, HIE grade 3 or more, cord PH at delivery

In order to evaluate the associations between cervical stiffness and the main outcome in the presence of other variables, we will capture the following data from electronic medical records; maternal age, body mass index at booking, ethnicity, neonatal weight, neonatal gender, gestational age at induction, indication for induction of labour.

**6.4 INTERIM ANALYSIS AND MONITORING**

As there are no formal hypotheses being tested, there are no formal stopping rules (other than safety) or mechanisms defined here to stop the study prior to the planned end of study. The study with have a study management group that will be able to review at regular intervals all accumulating data, with the responsibility of reviewing the recruitment of participants, the collection of all essential data and to assess participant safety.

**6.5 STATISTICAL METHODOLOGY**

Descriptive statistics will be generated and presented as means (SD), median (IQR) and frequency of observations (percentages) with 95% confidence intervals as appropriate.

Reliability assessment of the Pregnolia System using Cronbach’s alpha and descriptive statistics with 95% confidence intervals will inform best use of the triplicate CSI measurements. Specifically exploring whether the first, average, median or lowest measurement of the three readings should be utilised in further analysis and most importantly inform best use of the CSI results in clinical practice.

Diagnostic performance of cervical stiffness assessments using the Pregnolia System for IOL outcome will be demonstrated through receiver operating characteristic curves with area under the curve and 95% confidence intervals being calculated, as well as aiming to define the optimum cut-off value for predicting vaginal delivery.

Multivariate analysis will be performed using logistic regression, including CSI and other variables related to IOL outcome, such as maternal age, gestational age and maternal weight at booking(28). Results will be presented as odds ratios with 95% confidence intervals.

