**2. STUDY OBJECTIVES**

The CASPAR study has the following objectives;

1. To inform for the design of an appropriately powered study to assess the capability of this novel device for IOL prediction.
2. To explore the acceptability of the cervical stiffness assessment in patients undergoing IOL.
3. To obtain cervical stiffness measurements in primiparous women prior to term IOL to:
   1. Determine the reliability and best interpretation of triplicate measurements in this patient group.
   2. Explore any potential association between cervical stiffness assessment and vaginal delivery following IOL.
   3. Compare to BS assessments taken concurrently and explore the association with outcome of IOL.

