**3.1 STUDY PROCEDURES**

**3.1.1 Cervical Stiffness measurement**

Firstly, cervical stiffness will be measured via sterile speculum examination. The cervical stiffness is assessed by using the Pregnolia System, composed of an active component, the Pregnolia Control Unit and a disposable probe, the Pregnolia Probe. The device will be used according to its instructions for use. Briefly, the measurement location is inspected for any measurement contraindication (see 4.1.3 exclusion criteria) and excessive mucous is removed with a swab from the cervical surface. Next, the single-use, sterile Pregnolia Probe is placed on the anterior lip of the cervix at 12 o’clock position and a recording of cervical stiffness is generated over maximum 60 seconds (typically ̴15 seconds) and recorded as Cervical Stiffness Index (CSI) in mbar. The measurement is repeated 3 consecutive times without any time lag.

This procedure will be undertaken by a member of the research team trained in speculum examination and trained to use the Pregnolia system.

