**3.2 STUDY OUTCOME MEASURES**

**Feasibility Outcomes**

Our feasibility outcomes of interest relate to whether the study procedure is acceptable, participant recruitment is achieved, data collection is feasible, and cervical stiffness assessment fidelity is maintained with adequate reliability and safety(25).

Our feasibility outcomes will be defined as follows;

1. Recruitment rate
   1. Measured as proportion of participants recruited compared to total number approached for recruitment in the study period
   2. Reasons for non-participation collected
2. Participant acceptability of cervical stiffness assessment at IOL
   1. Qualitative questionnaire following assessment
   2. Number of participant withdrawals throughout the study duration
3. Adherence to protocol and data collection
   1. Measured as number of protocol deviations
   2. Missing data
4. Cervical stiffness fidelity
   1. Ability to obtain triplicate cervical stiffness measurements
   2. Triplicate measurement reliability

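### Cronbach's alpha is the only reliability coefficient named for choosing among first, average, median or lowest CSI reading, but it describes only the three-reading mean and cannot separate these options

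*Protocol*

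**What the plan says.** Section 6.5 (Statistical Methodology) plans a reliability assessment of the device "using Cronbach’s alpha and descriptive statistics with 95% confidence intervals will inform best use of the triplicate CSI measurements". The task is specific: "exploring whether the first, average, median or lowest measurement of the three readings should be utilised in further analysis". The result is also meant to "most importantly inform best use of the CSI results in clinical practice".

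The analysis serves the first sub-item of objective 3 in section 2, "Determine the reliability and best interpretation of triplicate measurements in this patient group". It also serves one of the two sub-items of the fourth feasibility outcome in section 3.2, "Triplicate measurement reliability".

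Section 3.1.1 describes how the readings arise. The probe is placed at the 12 o'clock position on the anterior lip, CSI is recorded in mbar, and "The measurement is repeated 3 consecutive times without any time lag".

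No ICC, within-woman SD, repeatability coefficient, reading-order analysis or target value for alpha is named. The descriptive statistics are described only generally, at the start of section 6.5 and in section 6.5.6. Neither place says that CSI will be summarised separately for readings 1, 2 and 3.

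**The concern.** The decision is a comparison of four ways to reduce three readings to one value. That needs to be informed by how much error a single reading carries, whether readings change systematically with order, and how large the error is in mbar. Alpha addresses none of these directly. It is one coefficient for the set of three, and it estimates the consistency of their sum or mean.

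An order effect is worth testing here because suction is applied three times in succession with no pause. The documents do not say that one exists.

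The chosen summary would be carried into the ROC analysis, the optimum cut-off, the logistic regression and, through objective 1, the design of the larger study. A reassuring alpha could be taken to mean that one reading is enough when single-reading agreement is only modest.

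**Working it through.** **Inputs.** From the protocol: k = 3 consecutive readings (section 3.1.1) and n = 100 women (section 6.5.1). It states no reliability figure, alpha threshold, CSI variance or drift, so there is no figure to reproduce. All reliability and drift values below are assumptions, shown as ranges.

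**1. What alpha measures.** alpha = [k/(k−1)] × [1 − (sum of the reading variances)/(variance of the sum)]. Only variances of the readings and of their sum enter, so adding a constant to every second or third reading changes nothing. Alpha equals the consistency ICC of the three-reading mean.

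**2. Single-reading reliability behind a given alpha.** With parallel readings (equal variances and covariances), alpha = 3r/(1 + 2r), where r is the single-reading ICC:
- r = 0.50: 1.5/2.0 = 0.75
- r = 0.60: 1.8/2.2 = 0.82
- r = 0.70: 2.1/2.4 = 0.88

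The inverse is r = alpha/(3 − 2 × alpha). For alpha = 0.80, r = 0.80/1.40 = 0.57. With n = 100, F-based 95% intervals are 0.72 to 0.86 for alpha and 0.46 to 0.67 for the single reading.

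**3. One alpha, four different reliabilities.** In a simulation of 200,000 women with parallel normal readings, no drift and alpha 0.80, the squared correlation with the true value was:

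| Summary | Reliability |
| --- | --- |
| Mean | 0.80 |
| Median | 0.749 |
| Lowest | 0.705 |
| First | 0.571 |

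**4. Readings that are not parallel.** Suppose only the first reading is noisy: true variance 1, error variances 1, 0.25 and 0.25. Its reliability is 1/(1 + 1) = 0.50, and that of the other two is 1/1.25 = 0.80. The reading variances sum to 2 + 1.25 + 1.25 = 4.5, and the variance of the sum is 9 + 1.5 = 10.5. So alpha = 1.5 × (1 − 4.5/10.5) = 0.857. Back-calculating a single-reading value gives 0.857/(3 − 1.714) = 0.67, against the true 0.50 for the first reading, which is one of the four candidates.

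**5. Drift.** Take between-woman variance 1 and r = 0.60, so error variance is 0.4/0.6 = 0.667. Let each reading shift by d between-woman SDs from the one before. The order positions 0, d and 2d have variance (d² + 0 + d²)/2 = d². The single-reading absolute-agreement ICC is then 1/(1 + 0.667 + d²):

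| Drift per reading (between-woman SD) | Alpha | Absolute-agreement ICC, single reading |
| --- | --- | --- |
| 0 | 0.82 | 0.60 |
| 0.25 | 0.82 | 1/1.729 = 0.58 |
| 0.5 | 0.82 | 1/1.917 = 0.52 |
| 1.0 | 0.82 | 1/2.667 = 0.375 |

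The fall means that readings at different positions are less interchangeable. It does not mean that a fixed position, such as always the first, ranks women less well: its consistency stays at 0.60. It matters for a cut-off in mbar and for comparing summaries that use different positions.

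**6. Would descriptive statistics show the drift?** At d = 0.5 the shift from reading 1 to reading 3 is 1.0 SD. The standard error of that paired difference is √(2 × 0.667/100) = 0.115, so the shift is 1.0/0.115 = 8.7 standard errors. At d = 0.25 it is 0.5/0.115 = 4.3. Mean CSI by reading order, or the mean paired change with its interval, would therefore reveal it if reported.

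**The case against.** The strongest reply is that the plan does not rest on alpha alone. The same sentence adds descriptive statistics with 95% confidence intervals, and step 6 shows that these would expose a sizeable drift if given by reading order. A reader might infer that the plan is blind to drift or cannot support its own decision. The documents do not support that: the blindness belongs to alpha. What remains is that no by-order summary is stated.

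Second, a single-reading value can be derived from alpha, so it would be wrong to say that alpha carries no such information. That stands, but only for parallel readings. The derivation is not planned, misses drift, and does not rank median against lowest if the parallel assumption fails.

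Third, the effect at small drift is slight (0.60 to 0.58 at 0.25 SD per reading), and no CSI data in the protocol point to drift. The silicone-model study described in section 1.1 found the device repeatable, although models do not settle how a native cervix responds. This stands, and is why the drift figures are only an assumed range.

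Fourth, the study is exploratory, sets no alpha threshold and tests no formal hypothesis, and triplicate reliability is one sub-item of one feasibility outcome. All three readings are to be taken from every woman, so better measures can be computed later. This limits the severity. It does not make alpha suitable for the task, and the protocol itself names alpha, so this is not merely detail left to an analysis plan.

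**Conclusion.** The point holds for the named coefficient and should be fixed. Alpha cannot discriminate among the four summaries, does not register a constant shift by reading order, and gives no error in mbar. A conventionally good value is compatible with modest single-reading reliability: 0.75 to 0.88 corresponds to 0.50 to 0.70 with parallel readings. On the assumed drifts of 0.25 to 1.0 between-woman SD per reading, alpha stays at 0.82 while single-reading absolute agreement falls from 0.60 to between 0.58 and 0.375.

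The algebra does not depend on CSI data, but the sizes do, and the protocol gives none. A reader might go further and infer that alpha will lead the team to adopt an unreliable single reading. The documents support only that it could: no decision threshold is set, and other descriptive statistics are planned.

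**What to change.** In section 6.5, make the following the primary reliability analysis:
- Mean CSI by reading order and mean change between readings, with 95% CIs, from a model with woman as random effect and reading order as fixed effect.
- Two-way absolute-agreement ICC for a single reading and for the mean of three, with 95% CIs.
- Within-woman SD and repeatability coefficient in mbar, with a check of whether error grows with CSI level.

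State that the choice among first, average, median and lowest will be based on these measures. Alpha may stay as an optional extra. The cost is one revised paragraph and a little more analysis of the same readings. No additional measurements or participants are needed.
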